### Ethics statement

Ethical approval has been obtained Mbale Regional Hospital Research Ethics committee (MRRH_REC 095/2017) and from Imperial College Research Ethics Committee (17IC3965), the sponsor of the study. The trial was registered on ISRCTN (ISRCTN49726849) on 27
^th^ October 2017 and updated on 12
^th^ August 2020 (detailing delay in start of trial and new start date).

### Safety

The randomised trial will be conducted in children who are most likely to benefit from the treatment. We will minimise the risks of cannula insertion and phlebotomy by pretrial training in phlebotomy technique and regular cannula site inspection which is included in a SOP. We have calculated that no more than 1ml/kg of blood will be drawn for research purposes at any one time.

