### Blood sampling schedule

Following consent and randomisation, blood samples will be taken for the following investigations: full blood count, urea and electrolytes, lactate, glucose, malaria status (malaria slide), blood culture and other clinically indicated investigations (not required by the study protocol). Urine will be taken as soon as possible after trial enrolment for multi-stick analysis for assessment of cola or red colour urine and additional storage for later analysis of gut barrier function. In accordance with national guidelines, HIV testing will be performed during admission procedures since this is one of the eligibility criteria. Pre- and post-test counselling will be done in accordance with routine practice. At admission, a venous blood sample will be collected into Heparin and EDTA tubes and stored for subsequent cytokine and biomarker assays, parasitological (
*P. falciparum* HRP2), genetic studies (including sickle cell and glucose-6-phosphatase deficiency status) and immune activation studies (transcriptome and cellular assays). For the latter, red and white cell pellets will be prepared and stored. Further blood samples will be taken at 72 hours, seven days and 28 days (for biomarker assays and immune activation studies); and at day seven for repeat blood culture (see
Table 3). Changes in inflammatory markers (including CRP and procalitonin, PCT) will be measured retrospectively at 72 hours and day seven and microbiology cure measured at day seven (from blood cultures and using non-culture based molecular diagnostics on stored blood).

**Table 3. T3:** Detailed laboratory investigation schedule.

Day from recruitment	D0	D1	D3	D7	D28
Blood culture	3 ml			3 ml (cases)	
PK studies (cases only)	2 x 0.25 ml			1 x 0.25 ml	
Whole blood (Endotoxin)	1.5 ml		1.5 ml	1.5 ml	
Whole blood EDTA (genetics)	1 ml				
Whole blood (transcriptomics, CRP, procalcitonin, calprotectin, gut barrier function)	4.5 ml		2 ml	2 ml	4.5 ml
**Total blood volume research**	**10.4 ml**	**0.5 ml**	**3.5 ml**	**7 ml**	**5 ml**
Urine	x	x	x		

PK, pharmacokinetics; CRP, C-reactive protein.

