### Clinical management and monitoring

All trial patients will receive standard of care including (intravenous or oral) anti-malarial drugs following national guidelines, based on WHO syndromic patient management
^
29
^. We will collect data on all administered drugs. Antipyretics, anticonvulsants and treatment for hypoglycaemia will be administered according to nationally agreed protocols. If required, maintenance fluids will be run at 3-4 ml/kg per hour irrespective of age until the child can drink and retain oral fluids. As the trial is designed to target the use of ‘appropriate’ antimicrobial treatments, clinicians will be free to prescribe antibiotics other than cephalosporins, quinolones or macrolides on admission day two based on the child’s clinical condition and according to country guidelines. On day three (or earlier if results available) clinicians will be permitted to prescribe broad-spectrum antimicrobials guided by the admission blood culture results (species and/or susceptibility). The Uganda severe malaria guidelines give no specific guidance on the use of antibiotics in severe malaria. Children or their carers will be provided with an appropriate supply of azithromycin drugs if discharged before day five.

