## Sub-studies

### PKPD study

For PK analysis, model-based sampling strategies will enable the description of both intra- and inter-patient variability. A maximum of 3x 0.2ml samples will be taken from each subject on two occasions between day one to five around meaningful time points to describe the PK throughout a dosing interval plus one sample at follow up on day seven to determine the elimination of azithromycin after end of treatment (a total of seven samples per patient). In the first year we will develop highly sensitive bioanalytical assays using ultra performance liquid chromatography coupled with tandem mass spectrometry (UPLC-MS) for determination of azithromycin in stored microvolumes of plasma (analysis performed at Radboud University, Nijmegen). 

Initially a population PK model will be developed for azithromycin and will investigate possible covariates for its PK. This will be followed by an investigation of the relationship between plasma PK and PD using the developed PK model, known MIC-values since the area under the curve (AUC):MIC ratio is the pharmacodynamic driver for azithromycin
^
16,
30
^ and the treatment outcomes (changes in CRP at day three and microbiologic cure and/or mortality at day seven). Based on Monte Carlo simulations, we expect that all dose groups should reach the population reference target (adult) AUC24h of at least 3.4 h*mg/L
^
24
^, although there are no data on absorption in severe malaria, which is characterised by impaired gut function
^
25
^, hence the need for this pilot. The different doses in 105 children provides variability in exposure so that we identify whether all doses are in the flat part of the exposure-response curve, in which case the lowest dose will be chosen. Other secondary endpoints include mortality at 48 hours, length of hospital stay (days), re-hospitalisation and other adverse events. Quality-control of stored bacterial isolates, non-culture (molecular) assessment of bacterial infection including the determination of MIC to inform PKPD studies will be batch-processed at KWTRP, Kenya.

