### Biomarker and gut barrier function

In 105 trial participants and 50 children with controls (severe malaria without Teule criteria) we plan to investigate from admission samples the utility of a range of potential biomarkers including CRP, PCT
^
31,
32
^ and endotoxin
^
25
^, to identify whether any of the above markers, alone or in combination, can predict which at-risk children with severe malaria have bacterial co-infections to improve the sensitivity of clinical/laboratory criteria and enable antimicrobial therapy to be further targeted. We will investigate associations between pathological concentrations of these markers and clinical, parasitological and microbiological data in cases (meeting Teule criteria) and controls (not meeting Teule criteria) to test their accuracy for stratification in the main trial. The samples will also allow us to analyse markers of gut barrier dysfunction – a requisite for bacteraemia (intestinal fatty acid binding protein (I-FABP) and the ileal-bile acid binding protein (I-BABP) and establish whether these can accurately predict children with blood-culture proven bacteraemia alone or in combination with clinical criteria/RDTs. In addition, we will analyse the peripheral blood mononuclear cell transcriptome in a subset of children with and without bacterial co-infection to verify the significant changes in transcriptome we observed in a small pilot study of children with malaria and bacterial co-infection compared to children with malaria alone and to confirm observed changes on the cellular level in a second set of children
^
33
^. We will investigate whether changes in gene expression profile can be translated into rapid and affordable biological tests predicting children with bacterial co-infection with high specificity and sensitivity. This later analysis is subject to additional funding.

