### Benefits

Children with severe malaria often develop complications such as convulsions, severe anaemia and hypoglycaemia which through close clinical monitoring will be identified at the earliest opportunity and appropriate therapy initiated. Mbale Regional Referral Hospital trial has considerable experience with managing severe malaria and this will serve to minimise the risks to the patients in the trial. Pretrial training of the dedicated study team will include specific training on general management of severe malaria and its complications. A manual of operations will provide clear management guidelines as well as the details of trial conduct and procedures. Children enrolled in the trial will therefore receive a higher quality of care than those managed routinely.

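### Taken as one admission draw, Table 3's printed day-0 volumes exceed the stated 1 ml/kg research-blood limit in the lightest children on the dosing chart

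*Protocol article*

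**What the plan says.** The Safety section gives a per-kilogram ceiling as the result of a calculation: "We have calculated that no more than 1ml/kg of blood will be drawn for research purposes at any one time". It makes no exception by weight or age.

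Table 3 (Blood sampling schedule) lists volumes by day from recruitment. At day 0 these are 3 ml for blood culture, 1.5 ml for endotoxin, 1 ml EDTA for genetics, and 4.5 ml in the row "Whole blood (transcriptomics, CRP, procalcitonin, calprotectin, gut barrier function". The last row falls to 2 ml at days 3 and 7. Two PK samples of 0.25 ml, in cases only, are also printed under day 0. The row "Total blood volume research" gives 10.4 ml for day 0.

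The status of the culture is not settled. The text above Table 3 lists "blood culture and other clinically indicated investigations (not required by the study protocol", and Clinical management and monitoring lets antibiotics be "guided by the admission blood culture results (species and/or susceptibility". Table 3 nevertheless places the culture above its research total.

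Table 1 begins with a 5.5-6.4 kg band. Cases are eligible from six months of age, and no minimum weight is stated.

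**The concern.** A limit per kilogram and a fixed volume in millilitres can both hold only above some body weight. The question is whether that weight lies below the lightest child the trial provides for. It does not: at 5.5 kg the limit allows 5.5 ml, and the printed day-0 research items come to more than that on every reading.

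What is at stake is a safety assurance, not an analysis. Haemoglobin below 5 g/dL is one of the qualifying severity criteria, so some of the children are severely anaemic. Ethics committees and readers will rely on a figure described as calculated, and it should follow from the schedule beside it.

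**Working it through.** **Inputs.** Limit: 1 ml/kg (Safety). Lowest weight: 5.5 kg (Table 1). Volumes: Table 3 as printed.

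**Formula.** Dose of blood drawn = volume / weight. Because the limit is 1 ml/kg, a fixed volume of V ml meets it only from V kg upwards.

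**The plan's own day-0 total.** Culture + endotoxin + genetics + whole blood = 3 + 1.5 + 1 + 4.5 = 10.0 ml. Adding PK (2 x 0.25 = 0.5 ml) gives 10.5 ml. The printed total is 10.4 ml, so Table 3's items reproduce it only approximately. They come close only with both the culture and the 4.5 ml tube included:
- without the culture: 7.0 ml, or 7.5 ml with PK;
- with the culture but a 2 ml tube: 7.5 ml, or 8.0 ml with PK.

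**PK samples.** They are printed under day 0, but the 0.5 ml total stands under day 1, where no item is listed. The PKPD study section says "A maximum of 3x 0.2ml samples will be taken from each subject on two occasions between day one to five". Leaving PK out of day 0 is therefore the more lenient reading, and the main figures do so.

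**Day 0, taken as one draw.**

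| Reading | Volume | ml/kg at 5.5 kg | Limit met from |
|---|---|---|---|
| Culture clinical, no PK | 1.5 + 1 + 4.5 = 7.0 ml | 7.0/5.5 = 1.27 | 7.0 kg |
| Culture clinical, with PK | 7.5 ml | 7.5/5.5 = 1.36 | 7.5 kg |
| Culture research, no PK | 10.0 ml | 10.0/5.5 = 1.82 | 10.0 kg |
| Culture research, with PK | 10.5 ml | 10.5/5.5 = 1.91 | 10.5 kg |
| Printed research total | 10.4 ml | 10.4/5.5 = 1.89 | 10.4 kg |

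The 7.0 ml reading exceeds the limit throughout the first dosing band (7.0/6.4 = 1.09 at its top) and in part of the second. The 10.0 ml reading exceeds it throughout the first four bands (10.0/9.4 = 1.06 at 9.4 kg) and in part of the fifth.

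**Other days, at 5.5 kg.**
- Day 7, cases, culture as research: 3 + 0.25 + 1.5 + 2 = 6.75 ml, or 1.23 ml/kg, above the limit below 6.75 kg. The printed 7 ml gives 1.27.
- Day 7, cases, culture as clinical: 0.25 + 1.5 + 2 = 3.75 ml, or 0.68 ml/kg.
- Day 7, controls (no culture or PK): 3.5 ml, or 0.64 ml/kg.
- Day 3: 3.5 ml, or 0.64 ml/kg.
- Day 28: 4.5 ml, or 0.82 ml/kg; the printed 5 ml gives 0.91.

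The conflict is therefore at day 0 on any reading, and at day 7 only for cases and only if the culture is research blood.

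**The case against.** The best defence is that Table 3 lists nominal volumes and that small children gave less. There is some support for this. The large tube includes transcriptomics, and the Biomarker and gut barrier function section plans that analysis of the "peripheral blood mononuclear cell transcriptome in a subset of children with and without bacterial co-infection". The same row is only 2 ml on later days. The Benefits section also says: "A manual of operations will provide clear management guidelines as well as the details of trial conduct and procedures". A condensed article may leave volume rules for small children to such a manual. With a 2 ml tube and a clinical culture, day 0 would be 1.5 + 1 + 2 = 4.5 ml, or 0.82 ml/kg at 5.5 kg, within the limit.

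A second defence is that the limit applies at any one time, whereas Table 3 is organised by day, so day-0 samples could be split. This bears most on the 10.0 ml figure, which needs the culture to be research blood and part of the same draw. It bears less on the 7.0 ml figure, because the text describes the stored heparin and EDTA samples as collected at admission.

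Both defences show that the limit could have been kept. Neither removes the conflict on the page, because nothing in the article ties the manual, the subset or a split draw to the volumes in Table 3.

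It is also fair to say that Table 3 is untidy: the day-0, day-7 and day-28 totals do not equal their items, and the PK entry and its total stand under different days. That limits how much weight the 10.4 ml figure can bear. The 7.0 ml figure does not depend on it.

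**Conclusion.** The stated maximum does not follow from the article's own schedule for the lightest children on the dosing chart. At 5.5 kg the day-0 figure is 1.27 ml/kg on the lenient reading, 1.82 with the culture counted as research, and 1.89 from the printed total. This assumes that the volumes apply to every child as printed and are drawn together at admission.

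Two stronger inferences are not supported. A reader might conclude that children were bled beyond the limit. The article reports no actual draws and no weights; 5.5 kg is a row in a dosing chart, not an observed child, so the number affected is unknown and could be zero. A reader might also take the 10.4 ml total as proof that the sponsor counts the culture as research blood. The total does come close only with the culture included, but no set of Table 3 items gives it exactly, and the text also treats the culture as part of clinical care.

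Severity is minor. No endpoint, sample size or analysis is affected.

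**What to change.** State whether the blood culture counts as research blood, and add a weight cap to Table 3. The Trial status section reports that recruitment and follow-up are complete, so first check what was done; a footnote on volumes should match actual practice.

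- **Culture clinical:** for example, reduce the day-0 whole-blood tube to 2 ml below 7 kg. This gives 4.5 ml, or 0.82 ml/kg at 5.5 kg. If the PK samples do belong to day 0, the reduction should start below 7.5 kg; the draw at 5.5 kg is then 5.0 ml, or 0.91 ml/kg.
- **Culture research:** reduce the tube to 2 ml below about 10 kg. This leaves 3 + 1.5 + 1 + 2 = 7.5 ml, which still exceeds the limit below 7.5 kg, so a further cut or a split draw is needed there (7.5 - 5.5 = 2.0 ml at 5.5 kg). At day 7, cases below 6.75 kg need the same treatment (6.75 - 5.5 = 1.25 ml at 5.5 kg).
- **Volumes not reduced in practice:** restate the maximum in the Safety section as about 1.3 ml/kg without the culture, or 1.8-1.9 ml/kg with it.

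The work is a check of the sampling procedure and one footnote or one corrected sentence. The price is either smaller stored samples for biomarker and transcriptome work in the lightest children, or a less favourable safety figure in print.

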### Benefits

Children with severe malaria often develop complications such as convulsions, severe anaemia and hypoglycaemia which through close clinical monitoring will be identified at the earliest opportunity and appropriate therapy initiated. Mbale Regional Referral Hospital trial has considerable experience with managing severe malaria and this will serve to minimise the risks to the patients in the trial. Pretrial training of the dedicated study team will include specific training on general management of severe malaria and its complications. A manual of operations will provide clear management guidelines as well as the details of trial conduct and procedures. Children enrolled in the trial will therefore receive a higher quality of care than those managed routinely.

## Plans for dissemination of the study outcomes

### Public engagement

Results from this trial will be disseminated locally through community meetings and national meetings with the wider healthcare professional community. These systems have been developed for dissemination of MRC FEAST and TRACT trial results and will be adapted to dissemination for the TABS PKPD trial.

### National and international policymakers

The site principal investigator has discussed the study with Ministry of Health staff. When the results are available, we will provide a summary briefing highlighting the trial results and what then next steps will be. Whilst the current study will go some way towards addressing whether azithromycin could be used as an adjunctive treatment in severe malaria a future trial should include a pragmatic design to ensure results are applicable to health services in Africa. The approach we propose may also have utility for syndromic management of other conditions, especially those whose clinical features overlap with severe malaria and in areas where microbiological diagnostic facilities are non-existent. 

## Discussion

Severe malaria remains a common cause of paediatric admission in many countries in Africa. Children who have bacterial co-infection are at high risk of poor outcome. Establishing which children with malaria are at greatest risk of bacteraemia is critical to pragmatically inform a policy for targeted antibiotic therapy that could substantially reduce malaria-associated mortality while minimising the risks of excess antibiotic prescribing. Short-course empiric therapy with early termination guided by culture results (to prevent development of resistance
^
35
^) is commonly practiced in high-income countries. However, poor microbiology services and overloaded health systems mean that this approach is not feasible in much of Africa and a trial designed around it would not be generalisable. Thus, in many parts of Africa antibiotic prescribing in children with severe malaria is highly variable across hospitals, with most physicians essentially using antibiotics “blind”, and thus are unable to follow WHO guidelines recommending stopping broad-spectrum antibiotics when bacterial infection has been ruled out. A more pragmatic approach would be to use a standard short-course of a moderately broad-spectrum antibiotic that is not already recommended for empiric use in a large number of other conditions with the potential for improving both early and post-discharge mortality. Relevant to a future trial and to current guidelines, is that many hospitals in Africa lack microbiological culture facilities, meaning best practice is not obvious given the clear threat posed by antimicrobial resistance
^
36,
37
^. To address this within the context of this study and to inform a future trial, we aim to investigate potential approaches (that may be generalizable in future) to targeting antibiotics where microbiological faciliaties are not present or reliable.

We favoured investigating azithromycin since one study found that almost 50% of bacterial isolates were resistant to the antibiotics most commonly recommended for empirical use
^
11
^. For NTS specifically, the efficacy of gentamicin is doubtful and susceptibility testing unreliable due to its intracellular nature
^
17,
38
^. Third generation cephalosporins (e.g. ceftriaxone) are the most widely used antimicrobials but resistance is becoming widespread. Moerover, few children will receive an ‘adequate’ therapeutic dose of cephalosporins, since NTS, the commonest cause of bacterial co-infection, requires ~seven days parenteral therapy thus requiring prolonged hospital stay (median four-five days) with economic implications. Further, adding a major new indication for third generation cephalosporins (severe malaria) risks substantially expanding their use, with downstream threats of AMR to a second-line antibiotic currently recommended for other common childhood diseases. Newer antimicrobials, apart from financial considerations, have similar concerns that over-use could lead to resistance. 

We therefore plan to study azithromycin because of its favourable microbiological spectrum, its inherent antimalarial and immunomodulatory properties and dosing and safety profile. Its long half-life is also likely to protect children at increased risk of NTS bacteraemia during the month following a malaria episode. At present pharmacological data are lacking on the correct dosage of oral azithromycin for treatment of bacterial co-infection in severe malaria in African children. The TABS trial will therefore conduct a Phase I/II trial comparing three doses of azithromycin: 10, 15 and 20 mg/kg (prescribed for feasibility by weight-bands) spanning the lowest to highest mg/kg doses demonstrated to be equally effective as parenteral treatment for other salmonellae infection. Treatment will be given over five days in children with severe malaria at highest risk of bacterial co-infection (meeting Teule criteria) in order to generate relevant PK data by sparse sampling during dosing intervals. The goal is to determine, via population PK modelling, the optimal azithromycin dose in severe malaria, and investigate associations between azithromycin exposure and potential mechanisms PKPD using change in CRP, a putative marker of sepsis at 72 hours (continuous) and microbiological cure (seven-day) (binary), alone and as a composite with seven-day survival, while providing preliminary data on longer-term survival (to day 90). We will also evaluate whether a combination of clinical, point-of-care diagnostic tests, and/or biomarkers can accurately identify the sub-group of severe malaria with culture-proven bacteraemia by comparison with a control cohort of children hospitalized with severe malaria but not meeting Teule criteria, at low risk of bacterial co-infection.

A future Phase III trial may therefore consider two strata: first comparing a pharmacologically-informed dosage of oral azithromycin to standard-of-care (largely third generation cephalosporins) in children at highest risk of bacterial co-infection and second comparing standard of care versus no antibiotics in children with severe malaria but minimal risk of bacterial co-infection to establish whether a policy for targeted antibiotic therapy could substantially reduce malaria-associated mortality while minimising the risks of excess antibiotic prescribing. Risk of co-infection could be determined by Teule criteria
^
11
^, but would also be informed by this pilot trial. The primary outcome would be mortality at either day seven, day 28 or day 90 mortality which is also be informed by this pilot trial (other timepoints would be secondary outcomes). Other secondary outcomes include mortality at 48 hours, length of hospital stay (days); subsequent hospital readmission; adverse events, faecal changes in antimicrobial resistance
^
34
^ and cost-effectiveness.

